### Study design and setting

2.1

Based on the International Society for Pharmacoeconomics and Outcomes Research's Good Research Practices dictates,^[21]^ the study is a multicenter and prospective observational comparative effectiveness research for the effectiveness of CT in patients with LBP. The patients with LBP are being recruited from 4 university-affiliated hospitals and 3 KM hospitals. A patient receives treatment according to their treatment plan. During or after the treatment, an 8-week study is conducted and a researcher assesses change in the patient's condition and cost of therapy thrice. In the final analysis, the merged data from the participants’ questionnaire responses, hospital medical records, and administrative data and Health Insurance Review and Assessment Service (HIRA) data will be compared between the CT and sole treatment (ST) groups. Figure 1 depicts the study design in a flow chart.

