#### Secondary outcome measurement

2.5.2

Secondary outcome is the evaluation of cost-effectiveness assessed from the cost per quality-adjusted life-years (QALYs), the incremental cost-effectiveness ratio (ICER), and the cost-effectiveness acceptability curve (CEAC).

The cost per QALYs is estimated based on the area under the curve method^[26]^ for each participant's quality of life data (e.g., the EQ-5D-5L and the EQ-VAS). The ICER represents the economic value of an intervention compared with an alternative. This is calculated by dividing the difference in total incremental cost by the difference in the chosen measure of health outcome or incremental effect.^[27]^ In CEAC, the horizontal axis represents the cost-effectiveness per ICER, and the vertical axis represents the probability of meeting that cost-effectiveness.^[28]^

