### Sample size rationale

2.6

The sample size was calculated by using the means (group 1 = 1.4, group 2 = 2.2) and standard deviations (sd 1 = 2.57, sd 2 = 2.76) from a previous study by NRS^[29]^ in the estimation equation^[30]^ via G-power program analysis (a 2-tailed, α = 0.05, β = 0.2). The result was 352, and the target number of inclusion was set at 360.

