### Statistical analyses

2.7

Outcomes will be compared between the main groups (CT and ST), which are stratified into 2 subgroups (acute or chronic^[31]^ and outpatient or inpatient^[32]^). The CT group is defined as those who receive treatments from both an MD and a KMD. The ST group is defined as those who receive only one form of treatment from either an MD or a KMD.

For analyzing categorical data, Chi-square tests and Fisher exact tests will be used. For analyzing continuous data, Student *t*-tests, analyses of variance, and Wilcoxon signed-rank tests will be used after normal distribution has been confirmed. For analyzing missing data, the per-protocol (PP) and intention to treat (ITT) will be used. In cases of missing completely at random data and missing at random data, as defined by Rubin,^[33]^ the ITT will be used to analyze missing values using a multiple imputation^[34]^ of the PP.

For all statistical tests performed in this study, a significance level of .05 and a 2-tailed confidence interval of 95% are set up. The Stata MP version 14 (Stata Corp LLC, Texas) and SAS version 9.4 (SAS Institute Inc, Cary, North Carolina) will be used for all statistical analyses.

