### Ethics and dissemination

2.8

This study has been approved by the Institutional Review Boards of Daejeon University Dunsan Korean Medicine Hospital (DJDSKH-18-BM-06), Gil Korean Medicine Hospital, Gachon University (18-104), Dongshin University Mokpo Oriental Hospital (DSMPOS18–2), Dongguk University Bundang Oriental Hospital (DUBOH-IRB 2018-0002), Design Hospital (P01-201806-21-001), Samse Korean Medical Hospital (P01-201807-21-004), and Gangdong Mokhuri Korean Medicine Hospital (P01-201807-21-011). The protocol of this study has been registered with the Clinical Research Information Service (KCT0002827).

Based on the Declaration of Helsinki, sufficient explanation and answer will be provided and the rights and welfare of the participants are guaranteed. All data are stored in a double locked device or safe, and the corresponding author will have access to the final data. The confidentiality of personal information and anonymity will be maintained. The findings of this study will be disseminated by a report published in a peer-reviewed journal.

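### The sole-treatment comparator pools MD-only and KMD-only care with no provider-specific contrast, so the CT effect and the ICER depend on an uncontrolled provider mix

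*Protocol article*

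**What the plan says.** The Statistical analyses section of the protocol article (2.7) fixes both groups: "The CT group is defined as those who receive treatments from both an MD and a KMD", and "The ST group is defined as those who receive only one form of treatment from either an MD or a KMD". It defines one contrast: "Outcomes will be compared between the main groups (CT and ST), which are stratified into 2 subgroups". Those subgroups are acute or chronic, and outpatient or inpatient. Provider type is not among them. Analysis of variance appears in the list of tests, but no three-group comparison is described.

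The Secondary outcome measurement section (2.5.2) introduces the cost-effectiveness ratio in general terms: "The ICER represents the economic value of an intervention compared with an alternative". With the groups as defined, the only alternative available is the pooled ST group.

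On how patients reach a group, Study design and setting (2.1) says "The patients with LBP are being recruited from 4 university-affiliated hospitals and 3 KM hospitals" and "A patient receives treatment according to their treatment plan". It gives no quota or weight by provider type. The limitations in the Discussion cover confounding and the representativeness of the institutions, but not the mixed comparator.

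**The concern.** ST holds two forms of care, one Western and one Korean, which may differ in effect and in cost. Their average stands for neither one unless CT differs from both by the same amount. If CT helps more relative to one than to the other, the pooled NRS difference moves with the proportion of each that happens to be enrolled, even if nothing about CT changes.

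More is at stake in the economic analysis. The study is meant to inform policy on collaboration, and a policy reader will want to know whether CT is worth its extra cost over each single-system pathway. If one sole treatment is both cheaper and at least as effective as CT, then CT is dominated. A ratio computed against the average of the two can still come out finite and favourable, and nothing in it reveals the dominance.

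**Working it through.** **1. The plan's own figure.** Inputs from Sample size rationale (2.6): "means (group 1 = 1.4, group 2 = 2.2", so the difference is 0.8 NRS points; SDs 2.57 and 2.76; two-sided alpha 0.05; power 0.80. The allocation ratio is not stated, and 1:1 is assumed.

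- Common SD = √[(2.57² + 2.76²)/2] = 2.667; standardised difference = 0.8/2.667 = 0.30.
- Normal approximation: n per group = 2(1.960 + 0.842)² × 2.667²/0.8² = 174.4, so 175 (350 in total).
- Noncentral t: 176 per group, 352 in total, which is exactly the stated result. At 180 versus 180, power is 81%.

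The sample size is arithmetically sound for the pooled contrast, so the point does not rest on a calculation error.

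**2. Dependence of the pooled effect on the mix.** Let w be the MD-only share of ST, and let d_M and d_K be the CT effects against MD-only and KMD-only. Then

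pooled difference = w·d_M + (1 − w)·d_K.

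This is free of w only if d_M = d_K. The document gives neither effect nor w, so the values below are assumed and serve as illustration only.

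| d_M, d_K (assumed) | w = 0.10 | 0.25 | 0.50 | 0.75 | 0.90 |
|---|---|---|---|---|---|
| 0.8, 0.8 | 0.80 | 0.80 | 0.80 | 0.80 | 0.80 |
| 1.2, 0.4 | 0.48 | 0.60 | 0.80 | 1.00 | 1.12 |
| 0.4, 1.2 | 1.12 | 1.00 | 0.80 | 0.60 | 0.48 |
| 1.6, 0.0 | 0.16 | 0.40 | 0.80 | 1.20 | 1.44 |

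**3. Dependence of the ICER on the mix.** In the same notation,

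pooled ICER = [w·ΔC_M + (1 − w)·ΔC_K] / [w·ΔE_M + (1 − w)·ΔE_K].

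Assume increments of 100 cost units and 0.010 QALY against MD-only, and 300 units and 0.004 QALY against KMD-only:

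- w = 0.10: 280/0.0046 ≈ 60,900 per QALY
- w = 0.50: 200/0.0070 ≈ 28,600
- w = 0.90: 120/0.0094 ≈ 12,800

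**4. Hidden dominance.** Assume mean cost and QALY of 500 and 0.100 for CT, 450 and 0.101 for KMD-only, and 480 and 0.080 for MD-only. KMD-only is cheaper and more effective than CT, so it dominates. A 50/50 pool has cost (450 + 480)/2 = 465 and QALY (0.101 + 0.080)/2 = 0.0905. The pooled ICER is (500 − 465)/(0.100 − 0.0905) = 35/0.0095 ≈ 3,700 per QALY, with no sign that CT is dominated. Swapping the provider labels gives the mirror case.

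**5. What separate contrasts could deliver.** Assume 180 CT and 180 ST patients, difference 0.8, SD 2.667 and two-sided alpha 0.05. The half-width of the 95% interval is 1.96 × 2.667 × √(1/180 + 1/n).

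| Component's share of ST | n | Power | Half-width (NRS points) |
|---|---|---|---|
| 10% | 18 | 23% | 1.29 |
| 25% | 45 | 43% | 0.87 |
| 50% | 90 | 64% | 0.67 |
| 90% | 162 | 79% | – |
| Whole ST group | 180 | 81% | 0.55 |

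Powering both contrasts at 80% would take three groups of 176 (528 in total), which is beyond the target of 360.

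**The case against.** The strongest reply is that the pooled contrast answers the question asked. The Abstract states the aim as CT against ST, and the policy issue in the Introduction is joint coverage and the consultant fee. A payer setting a coverage rule can reasonably compare joint users with users of one system or the other. This stands, and it is why the pooled comparison should remain primary.

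A second reply is that secondary contrasts and group counts are usually left to an analysis plan. That holds for the layout of tables. Here, however, the protocol itself fixes the comparator, the single contrast and the subgroups, and provider type is absent from all three.

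A third reply is that every effect, cost and share above is assumed, and that with equal components the mix changes nothing. This is true. Only the algebraic dependence is established, not its size in this study.

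A reader might go further and infer that the blend is fixed by the site mix and is mostly KMD-only, since six of the seven approving institutions have Korean medicine, Korean medical or Oriental in their names (for example "Dongguk University Bundang Oriental Hospital"). The count is right, but the inference fails. A hospital's name does not show who treats its ST patients, recruitment per site is not given, and the Discussion describes the institutions as active in CT, so care from both professions is available there. Patient choice and enrolment also set the weights. Six of seven names cannot be turned into 86% of patients.

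**Conclusion.** The concern holds in a limited form. The protocol pools two kinds of sole care and plans no contrast of CT with either. The clinical difference and the ICER are therefore averages over a provider mix that the design does not control. For the NRS difference the mix drops out only if both component effects are equal; for the ICER, only if the component increments in cost and effect are equal or, more generally, give the same ratio. A pooled ICER cannot show whether one sole treatment dominates CT.

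The size is unknown. Under the assumed effects of 1.2 and 0.4 points, the pooled difference spans 0.48 to 1.12 around the planned 0.8 as the MD-only share goes from 10% to 90%; with equal effects it does not move. The documents do not show that pooling is wrong for the stated aim, that either component prevails, or that the two effects differ. This is an improvement that should be made, not a flaw that invalidates the primary comparison.

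**What to change.** Keep pooled CT versus ST as the primary comparison, with the sample size unchanged. Add to the plan, before outcome data are seen:

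- secondary, estimation-only contrasts of CT versus MD-only and CT versus KMD-only, with 95% intervals, for NRS, cost and QALY;
- a full incremental analysis over the three options (CT, MD-only, KMD-only), reported beside the pooled ICER;
- the MD-only and KMD-only counts, so that the weights behind the pooled figures are visible.

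No new collection should be needed. Section 2.4 describes the HIRA modality only as CT or ST, but applying the section 2.7 definitions already requires knowing which profession treated each patient. The team should confirm that this field is kept for ST patients.

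The cost is extra analysis and lower precision, worst in the smaller component. The separate contrasts should be labelled as estimates, not powered tests, and a three-option ICER resting on a small component should be shown with its uncertainty. They also carry the same confounding as the main comparison, since provider type may go with hospital.

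### Section 2.7 names equal-variance tests although usual care sets the CT and ST group sizes, so the 5% level and 95% intervals hold only if the groups turn out nearly equal in size or variance (minor)

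*Protocol article*

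**What the plan says.** The protocol article, section 2.7 (Statistical analyses), gives the rule for continuous outcomes. It opens by naming the test, "For analyzing continuous data, Student *t*-tests", and reads in full: "For analyzing continuous data, Student *t*-tests, analyses of variance, and Wilcoxon signed-rank tests will be used after normal distribution has been confirmed". Normality is the only condition attached; equality of variances is not mentioned. For all tests, "a significance level of .05 and a 2-tailed confidence interval of 95% are set up".

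Section 2.6 (Sample size rationale) plans on the NRS with "means (group 1 = 1.4, group 2 = 2.2" and "standard deviations (sd 1 = 2.57, sd 2 = 2.76) from a previous study by NRS", under "a 2-tailed, α = 0.05, β = 0.2". It concludes: "The result was 352, and the target number of inclusion was set at 360".

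Section 2.1 (Study design and setting) says that treatment follows each patient's own plan. The Discussion adds that the researchers have no hand in allocation. The text of the article gives no CT:ST ratio, quota or expected split.

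**The concern.** Student's t-test and ordinary analysis of variance use a single pooled variance. That is harmless when the groups are equal in size, or when their variances are equal. When neither holds, the pooled standard error is too small if the smaller group is the more variable one, and too large if the larger group is. The test then rejects a true null too often or too seldom, and the confidence interval is too narrow or too wide.

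The design guards against neither condition:

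- **Size.** CT and ST numbers follow from usual care. The sample size of 352 rests on equal groups, and no stated feature of the design delivers them.
- **Variance.** In a randomised trial, a null of no effect on any patient would also imply equal variances. That argument is not available for groups formed by treatment choice. The ST group also combines patients seen only by an MD with patients seen only by a KMD. The only two SDs in the article differ, if slightly.

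At stake is whether the stated level and coverage apply to the four primary measures. The direction of any error would be known only once the group sizes and SDs are seen.

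**Working it through.** **Inputs.** From section 2.6: SD₁ = 2.57, SD₂ = 2.76, difference in means 2.2 − 1.4 = 0.8, two-sided α = 0.05, power 80%, N = 360. The CT:ST splits below are assumptions, because the article gives none.

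**Step 1: reproduce the plan's figure.** The root-mean-square SD is √((2.57² + 2.76²)/2) = √((6.6049 + 7.6176)/2) = √7.1113 = 2.667, so d = 0.8/2.667 = 0.300. The normal approximation gives n = 2 × (1.960 + 0.842)² × 7.1113/0.64 = 174.4, that is 175 per group or 350 in all. The noncentral t calculation gives 176 per group, a total of 352 with 80.1% power. The stated 352 is therefore reproduced exactly, and it presupposes a 1:1 split.

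**Step 2: how far apart the SDs are.** SD ratio 2.76/2.57 = 1.074; variance ratio 1.153.

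**Step 3: pooled against true standard error.**

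- Pooled: SE²ₚ = s²ₚ(1/n₁ + 1/n₂), where s²ₚ has expectation [(n₁ − 1)SD₁² + (n₂ − 1)SD₂²]/(n₁ + n₂ − 2).
- True: SE² = SD₁²/n₁ + SD₂²/n₂.
- Large-sample type I error: 2Φ(−1.96 × SEₚ/SE).

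*270 patients with SD 2.57, 90 with SD 2.76:* s²ₚ = (269 × 6.6049 + 89 × 7.6176)/358 = 6.857; SE²ₚ = 6.857 × (1/270 + 1/90) = 0.1016; SE² = 6.6049/270 + 7.6176/90 = 0.1091. The ratio of standard errors is 0.965, the effective critical value 1.891, and the type I error 5.9%.

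*90 patients with SD 2.57, 270 with SD 2.76:* s²ₚ = 7.366; SE²ₚ = 0.1091; SE² = 0.1016. The ratio is 1.036, the effective critical value 2.031, and the type I error 4.2%.

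**Step 4: the range of splits.** The exact conditional rejection probability was averaged over 2,000,000 simulated pairs of sample variances, with Welch's test on the same draws.

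| Split (N = 360) | Student, larger group more variable | Student, smaller group more variable | Welch |
|---|---|---|---|
| 180/180 | 5.0% | 5.0% | 5.0% |
| 240/120 (2:1) | 4.5% | 5.6% | 5.0% |
| 270/90 (3:1) | 4.2% | 5.9% | 5.0% |
| 288/72 (4:1) | 4.1% | 6.0% | 5.0% |
| 324/36 (9:1) | 3.8% | 6.4% | 5.0% |

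The large-sample formula of step 3 agrees with this at 2:1, 3:1 and 4:1 to within 0.1 percentage point. Interval coverage is the complement: at 3:1, for example, 95.8% or 94.1%.

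**The case against.** The strongest reply is that nothing is shown to be wrong at the one split the article implies. At 1:1 the level is 5.0% and coverage 95.0%. Observing treatment rather than assigning it does not rule out recruiting similar numbers of each kind of patient, and the flow chart, which might show group targets, is not available here. This stands: a reader might infer that the stated error rate is simply false, and the documents do not support that.

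Nor do the SDs prove unequal variances. They are estimates from an earlier study of unstated size and differ by about 7%. If that study had about 176 patients per group (an assumption), a variance ratio of 1.15 would lie within sampling error (two-sided p about 0.35). Section 2.6 also does not say which of its two groups corresponds to CT. This stands too.

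A reader might infer much larger distortions for other outcomes. At 288/72, an SD ratio of 1.25 would give about 8.7% or 2.5%, and a ratio of 1.5 about 12.2% or 1.4%. Those ratios have no source in the article, which gives no SD for ODI, EQ-5D-5L or EQ-VAS, so these figures are only illustrations. Extending the point to costs is not supported either, because the article does not say that its economic outcomes are tested by t-test.

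Finally, the variance option can be called a detail for the analysis plan. That carries some weight, since the article never uses the word pooled. But it does name the test, and the usual meaning of that name is the equal-variance form. If Welch is intended, the same edit makes that clear.

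**Conclusion.** The point holds in a conditional form and is minor. The tests named in section 2.7 keep their stated level and coverage only if the CT and ST groups turn out nearly equal in size or in variance, and the design secures neither. On the plan's own SDs the departure is about one percentage point in either direction up to 4:1, about 1.4 points at 9:1, and zero at 1:1. These figures rest on the assumed splits and on the earlier study's SDs carrying over to this one. The error may be conservative as well as anti-conservative. The case for acting is that its direction cannot be known in advance, and that a test which holds 5.0% at every split examined is available at essentially no cost.

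**What to change.** In section 2.7, name Welch's unequal-variance t-test for the independent between-group CT v ST comparisons of NRS, ODI, EQ-5D-5L and EQ-VAS, and Welch's analysis of variance where more than two independent groups are compared. State that the choice is fixed in advance and does not depend on a preliminary test of variances.

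Limit the change to between-group comparisons. Patients are assessed three times, and the listed methods may also serve paired or within-patient analyses. Welch's test does not apply to those, and their wording should stay.

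The cost is one or two sentences. Both named packages offer the option, and essentially nothing is lost when sizes and variances are equal. The sample size calculation need not change on this account.

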**Method/design::**

This multisite, prospective observational comparative effectiveness research study is part of a nationwide pilot project for KM and WM collaboration launched by the Korean Ministry of Health and Welfare. The duration of the study is 8 weeks, and the target number of inclusion is 360 patients. Participants receive treatment according to their treatment plan, and a researcher conducts investigations thrice, every 4 weeks. In the final analysis, the merged data from the participants’ questionnaire responses, hospital medical records, and administrative data, and Health Insurance Review and Assessment service data will be compared between the CT and ST groups.

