#### Primary outcome measurement

2.5.1

Primary outcome is the evaluation of clinical effectiveness assessed from the change in the numeric rating scale (NRS), Oswestry Disability Index (ODI), EuroQol-5 dimension-5 level (EQ-5D-5L), and EuroQol-visual analog scale (EQ-VAS) scores.

The NRS^[22]^ converts pain intensity to numerical values, using a horizontal line between 0 (no pain) and 10 (greatest pain severity). The ODI^[23,24]^ measures the degree of daily life disability caused by LBP. The EQ-5D-5L^[24,25]^ measures the quality of life using questions on mobility, self-care, activity, pain intensity, depression, and anxiety. The EQ-VAS^[25]^ scores quality of life using a horizontal line.

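### The CT–ST comparison of clinical change is committed to t-tests and unspecified ANOVA, with no baseline adjustment, no stated use of the three visits and no visit that defines the change

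*Protocol article*

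**What the plan says.** The Abstract (Method/design) states that over the 8-week study "a researcher conducts investigations thrice, every 4 weeks". Section 2.1 repeats that "a researcher assesses change in the patient's condition and cost of therapy thrice".

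Section 2.5.1 begins "Primary outcome is the evaluation of clinical effectiveness assessed from the change in the numeric rating scale (NRS" and goes on to the ODI, EQ-5D-5L and EQ-VAS. It gives no visit for the change.

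Section 2.7 compares the CT and ST groups, with strata for acute or chronic pain and for outpatients or inpatients. For continuous data it commits to Student t-tests, "analyses of variance, and Wilcoxon signed-rank tests will be used after normal distribution" has been confirmed. It names no covariate, no repeated-measures or mixed model, and no primary time point. Missing values that are missing completely at random or at random are to be multiply imputed.

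Two other places bear on the point. Section 2.5.2 uses the serial quality-of-life data for QALYs: "The cost per QALYs is estimated based on the area under the curve method". The Discussion (section 3) concedes that allocation is not randomised and that confounding may be present.

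**The concern.** The named tests leave three things unsettled for the primary comparison.

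- **Baseline.** A t-test of raw change subtracts the whole baseline value, whatever its correlation with follow-up. Unless that correlation is very high, this adds noise. In a non-randomised study it also matters for bias: a group that starts with worse pain tends to improve more through regression to the mean alone. The strata in section 2.7 do not adjust for the baseline score.
- **Visits.** Two follow-up values per patient are collected, but nothing says whether one or both enter the comparison, or how their correlation is handled. The signed-rank test is paired. It can compare two visits within a patient but does not by itself contrast CT with ST.
- **Time point.** With no visit named, the week-4 change, the week-8 change or both could be reported as the primary result.

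At stake are precision that data already collected could supply, and a CT–ST difference that may partly reflect where the groups started.

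**Working it through.** **1. The plan's own figure.** Section 2.6 gives "means (group 1 = 1.4, group 2 = 2.2") and "standard deviations (sd 1 = 2.57, sd 2 = 2.76"), two-sided α = 0.05 and β = 0.2.

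- Difference: 2.2 − 1.4 = 0.8.
- Pooled SD: √((2.57² + 2.76²)/2) = 2.667. Standardised difference: 0.8/2.667 = 0.300.
- A two-sample t-test with equal groups (assumed, as the ratio is not stated) needs 176 per group, or 352 in total, with power 80.1%. This matches the stated 352.

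The sample size therefore rests on one value per patient.

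**2. Precision of raw change against a baseline-conditional analysis.** The documents give no between-visit correlation ρ, so 0.3, 0.5 and 0.7 are assumed. With equal variances at the visits (set to 1) and baseline unrelated to group:

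- Variance of change: 2(1 − ρ)
- Variance of follow-up given baseline: 1 − ρ²
- Ratio: (1 − ρ²)/(2(1 − ρ)) = (1 + ρ)/2

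| ρ | change | given baseline | ratio |
|---|---|---|---|
| 0.3 | 1.40 | 0.91 | 0.65 |
| 0.5 | 1.00 | 0.75 | 0.75 |
| 0.7 | 0.60 | 0.51 | 0.85 |

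The standard error falls to √ratio = 0.81, 0.87 and 0.92 of that for raw change.

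If baselines differ between equal groups by δ within-group SDs, the adjusted variance is multiplied by 1 + δ²/4. For an assumed δ = 0.3 that is 1.0225, and the ratios become 0.66, 0.77 and 0.87. The gain survives a moderate imbalance.

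**3. What the week-4 values add.** Given baseline, and with equal correlations between all visits, the two follow-ups correlate r = ρ/(1 + ρ) = 0.23, 0.33, 0.41. If 15% (assumed) are missing at week 8, using their week-4 values multiplies the variance of the baseline-adjusted week-8 contrast by 1 − 0.15r² = 0.992, 0.983, 0.975. That is a gain of about 1–3%. Nearly all the precision comes from conditioning on baseline.

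**4. Regression to the mean.** Suppose follow-up given baseline is the same in both groups (no treatment difference) with slope ρ. The expected change is then a constant minus (1 − ρ) times the group's baseline mean, so a baseline gap g shifts the CT–ST difference in raw change by (1 − ρ)g in absolute size. The baseline gap is not in the documents and is assumed:

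| gap g (NRS points) | ρ = 0.3 | ρ = 0.5 | ρ = 0.7 |
|---|---|---|---|
| 0.5 | 0.35 | 0.25 | 0.15 |
| 1.0 | 0.70 | 0.50 | 0.30 |

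These shifts stand against the difference of 0.8 on which section 2.6 sizes the study.

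**The case against.** **The article condenses a fuller plan.** No SAP is shown, Table 1 (the collection schedule) is not visible, and a covariance structure or longitudinal model is commonly left to the SAP. This stands as far as silence goes. But section 2.7 is not silent: it says which tests will be used. The point is aimed at that commitment.

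**A t-test on one change score is a legitimate 5% test.** As regards within-patient correlation, this is correct. A reader might infer that the three visits will be pooled as if independent and that the false-positive rate is inflated. The documents do not support that. Nothing plans pooling, the outcome is change, and 352 reproduces from one value per patient. ANOVA is unqualified and could be a repeated-measures ANOVA, and the signed-rank test is itself paired.

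**The follow-up data are not simply thrown away.** QALYs use the serial EQ-5D-5L and EQ-VAS values, and the planned imputation could draw on week-4 values when week 8 is missing. A comparison with a complete-case t-test would therefore misrepresent the plan.

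**Baseline adjustment is not neutral here.** This is the strongest objection, and it stands in part. Without randomisation, adjusted and raw-change analyses estimate different contrasts when baselines differ. Adjustment is right if baseline severity itself influences treatment choice and later pain. Raw change is right if the groups differ by a stable amount that would have persisted. The choice rests on a causal assumption, which is a reason to state it in advance and show both.

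**Conclusion.** The point holds as a weakness in the chosen method and as an undefined time point. It does not show an invalid test.

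Replacing raw change with a baseline-conditional analysis lowers the variance to about 0.65, 0.75 or 0.85 at assumed correlations of 0.3, 0.5 or 0.7, given equal variances across visits and baseline unrelated to group. The repeated-measures part adds little precision. Its value is that it gives both follow-ups one coherent analysis. The potential shift from regression to the mean is sizeable against the planned 0.8 (0.15 to 0.70 points over the assumed range), but it depends on a baseline gap that is not yet known.

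A reader might also turn the variance ratio into a power gain over the stated 80%. That does not follow, because section 2.6 does not say that its SDs are those of change scores. Baseline adjustment deals with one measured imbalance. It does not remove the confounding that the Discussion acknowledges.

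**What to change.** For each of NRS, ODI, EQ-5D-5L and EQ-VAS, replace the t-test/ANOVA with one linear mixed model for repeated measures:

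- responses: the week-4 and week-8 values;
- fixed effects: group, visit, group-by-visit and the baseline value;
- unstructured within-patient covariance;
- any confounder or hospital terms entered in this same model.

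Report the CT–ST contrast at both visits and name one visit's contrast as primary in sections 2.5.1 and 2.7. Keep the raw-change comparison as a sensitivity analysis, and state what each analysis assumes about baseline differences between the groups.

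The cost is wording and a standard procedure in the SAS and Stata versions already named; no new data are needed. Two downsides should be stated: the model relies on missing-at-random, which the plan already assumes for its imputation, and its contrast will differ from the raw-change contrast when CT and ST start at different levels.
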